## Methods/design

### Study aim

Our primary aim is to assess the effectiveness of an innovative package of orienting doctors and community health workers (CHW) about community perceptions on CAP barriers to qualified health care seeking plus infrastructural strengthening by (i) providing “Pneumonia Drug Kit” (PDK) (ii) establishing “Pneumonia Management Corner” (PMC) at additional primary health center (APHC) and (iii) “Pneumonia Management Unit” (PMU) at Community health center (CHC) *ALONG* with one of the 4 different behavior change communication (BCC) interventions:Intervention 1: Organizing Childhood Pneumonia Awareness Sessions (PAS) for caregivers of children < 5 years of age during a routine immunization day, using self-developed and validated Information, Education and Communication (IEC) materials, in PHCs and CHC monthly, conducted by a trained Auxillary Nurse Midwife (ANM) and project facilitators.Intervention 2: Organizing PAS on Village Health and Nutrition Day (V.H.N.D.) once a month by the Accredited Social Health Activist (ASHA) trained to conduct such sessionsIntervention 3: Combination of Both Intervention 1& 2Intervention 4: Usual Care

Outcome measure will be number of CAP treated by ANMs/doctors with medicines from PDK or treated at either PMC or PMU in interventions given by ANMs/ASHA workers.

Our second objective is to ascertain change, if any, in the types of health care providers’ service utilization for Acute Respiratory Illness (ARI)/CAP in last 12 months in children less than 5 years pre and post intervention.

Outcome measure will be number of ARI/CAP Treated by ANMs/doctors by various health care providers in the past 12 months in interventions given by ANMs/ASHA workers.

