Univariate distribution of baseline and outcome variables would be assessed by frequency counts. Outliers will be identified, reported and excluded from analysis if required. They would be compared between interventions using chi square test for categorical and Student’s t test and ANOVA for continuous variables. A *p* value of < 0.05 will be taken as statistically significant, using a two tailed distribution. Adherence to the intervention across each arm will be calculated and compared across the three arms (as one was a control arm). Good intervention is defined as > 75% adherence to the sessions in the duration of the project. Primary outcomes will be number of PDK kits distributed to children plus the number of children treated by government functionaries for acute respiratory infection (ARI) or pneumonia without PDK, using medicines available at the health facility in interventions given by ANMs/ASHA workers. If we find that the diagnosis of children being treated is not mentioned, then we fill this missing information by extrapolation from data where diagnosis is given for the same month and within the intervention arm, assuming that there would be similar proportion of cases with this diagnosis. We will compute the difference in the proportion of ARI/pneumonia treated in each intervention arm when compared to control arm in the intention to treat analysis. For the secondary outcome, we will compare the proportion of cases with ARI/pneumonia treated by government providers as their first choice in interventions given by ANMs/ASHA workers, as an intention to treat analysis. In the per-protocol analysis we will compare the proportion of cases with ARI/pneumonia treated by government providers as their first choice in interventions given by ANMs/ASHAs from those households which have participated in the baseline as well end line survey using paired t-test. As a sub-analysis, we will compare the mean, median and interquartile range of out of pocket expenditure for ARI/pneumonia in the baseline and end line survey within each arm. As a comparator, we will do similar analysis for cases who have suffered from diarrhea to assess whether changes in spending were a function of time or because of care seeking from government providers, which is most inexpensive.

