A qualitative narrative of the process of establishment of the project will be given. Key informant and semi-structured interviews will be used to assess the level of satisfaction of stakeholders with (a) the services provided by public health facility augmentations and (b) IEC campaign strategies. Qualitative analysis techniques will be used for this data analysis.

Primary outcomes will be (a) number of patients of CAP treated by ANMs/doctors with medicines from PDK OR treated PMC OR PMU and (b) health service providers’ preference for treatment of CAP/ARI. For health facility utilization, the data will be abstracted periodically from the records maintained there. Feedback will be given to each facility on the process indicators within a month. For health provider preference, data from base line and end-line multistage cluster surveys will be used. At the end of the project the primary outcome measures will be compared in interventions given by ANMs/ASHA workers, using tests of proportion.

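### The primary outcome is stated in incompatible ways, and provider choice is both secondary and primary, so the text leaves the headline outcome open

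*Protocol article*

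**What the plan says.** The protocol article describes its main outcome in several places.

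- **Abstract and Study aim.** Both count pneumonia cases only. Study aim reads: "Outcome measure will be number of CAP treated by ANMs/doctors with medicines from PDK or treated at either PMC or PMU". It then adds provider use as a separate aim: "Our second objective is to ascertain change, if any, in the types of health care providers’ service utilization".
- **Data management & analysis plan, paragraph on statistical tests.** The text here is: "Primary outcomes will be number of PDK kits distributed to children plus the number of children treated by government functionaries for acute respiratory infection". The second term of this sum also takes in pneumonia and is limited to children who received no kit and were given the facility's own drugs. The same paragraph continues: "For the secondary outcome, we will compare the proportion of cases with ARI/pneumonia treated by government providers as their first choice".
- **Data management & analysis plan, later paragraph.** The text here is: "Primary outcomes will be (a) number of patients of CAP treated by ANMs/doctors with medicines from PDK OR treated PMC OR PMU". A further item is listed alongside it as a second primary: "and (b) health service providers’ preference for treatment of CAP/ARI". The source of that second item is given as: "For health provider preference, data from base line and end-line multistage cluster surveys will be used".
- **Post intervention phase.** Primary measures are mentioned only by example (use of public facilities for CAP, from the facility audit). Community preference for providers is described separately, under the end-line survey.

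The analysis section sets significance at p < 0.05, two-tailed, and compares each intervention arm with control. It does not rank the outcome statements.

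**The concern.** A primary outcome has to be one thing, fixed in advance. Here a count restricted to pneumonia and a count that takes in any ARI are each called primary, and a survey measure moves between secondary and primary. This is a conflict within the published text, not detail left to an analysis plan that is not shown. A later plan could choose between the statements, but the protocol would still contradict itself.

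Two things are at stake. First, a reader of the results could not tell from the protocol which outcome was meant to carry the conclusion. Registration was retrospective, so the registry is a weaker independent check than usual; its content is not available here. Second, the result is meant to guide policy. Post intervention phase plans state-wide scale-up of the most effective communication strategy, and which strategy looks best may depend on which count is used.

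**Working it through.** The protocol article states no sample size, power or event figure for these outcomes, so there is no figure to reproduce. The check is a comparison of texts, followed by two illustrations.

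**Step 1: the definitions side by side**

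| Place | Condition | What is counted | Called |
|---|---|---|---|
| Abstract; Study aim | CAP only | cases treated with a kit, or at a corner or unit | outcome of the primary aim |
| Analysis section, statistical-tests paragraph | ARI or pneumonia | kits given out plus children treated without a kit from facility medicines | primary |
| Analysis section, later paragraph, (a) | CAP only | as in Study aim | primary |
| Analysis section, later paragraph, (b) | CAP/ARI | provider preference, from surveys | primary |

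The second row differs from the first in three ways: it admits ARI that is not pneumonia, it adds kits to children, and it drops the condition of treatment at a corner or unit.

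**Step 2: the role of provider choice.** It is the second objective in Study aim, secondary in the statistical-tests paragraph and primary in the later paragraph. The wording varies (government provider as first choice; provider preference), but both concern which provider treats ARI or CAP.

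**Step 3: can the two counts disagree?** Let s be the pneumonia share of the wider count, a the relative change in pneumonia treated, and b the relative change in other ARI treated. Treating the CAP count as the pneumonia part of the wider count, the relative change in the wider count is s × a + (1 − s) × b. The document gives no value for s; 5% to 30% is an assumption.

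- a = 30%, b = 0: 0.05 × 30% = 1.5%; 0.10 × 30% = 3%; 0.30 × 30% = 9%.
- a = 30%, b = 30%: 30% for any s, so no dilution.
- a = 0, b = 10%: 0.95 × 10% = 9.5% (s = 5%); 0.70 × 10% = 7% (s = 30%). The wider count rises with no change in pneumonia treated.

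The counts agree only if care-seeking for pneumonia and for other ARI moves together.

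**Step 4: what a free choice of headline outcome could cost.** Take one arm-versus-control contrast, no true effect, and valid tests at two-sided 0.05 with equal correlation between outcomes. One fixed outcome gives a false-positive chance of 0.05. In simulation, the best of two candidates gives about 0.095 at correlation 0.3 and 0.070 at 0.9. The best of three gives about 0.136 and 0.084. The correlations are assumptions, and the effect of allocating whole blocks is ignored.

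**The case against.** The strongest reply is that much of what one might build on this conflict does not follow from the text. Most of that reply stands, but it leaves the conflict itself untouched.

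- **Double counting.** A reader might infer that a child given a kit and later treated at a health centre enters the kits-plus-ARI sum twice. As worded, the second term covers treatment "or pneumonia without PDK, using medicines available at the health facility", so the two terms exclude each other. Duplicate records could still arise, but that is a data-capture risk and applies equally to the CAP count.
- **Family-wise error of 26% or 14%.** A reader might compute these from two outcomes by three contrasts (1 − 0.95^6) or from three contrasts (1 − 0.95^3). Both treat the contrasts as independent, whereas all three share one control arm. With equal arms the figures are nearer 23% (two independent outcomes) and 12.5% (one outcome). Silence on multiplicity is, besides, something an analysis plan commonly settles.
- **Dilution as a fact.** A reader might infer that including ARI necessarily weakens the effect. That requires care-seeking for other ARI to stay unchanged. The rationale section expects the package to build trust in public facilities generally, so other ARI attendance could rise too.
- **The CAP count has its own costs.** The analysis section expects some missing diagnoses and fills them from the same month and arm. A CAP-only count must separate pneumonia from other ARI, so it probably leans on that step more than the wider count does.
- **Actual selection.** The text shows that a choice is possible, not that anyone made one after seeing data.

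**Conclusion.** The concern holds as a contradiction over the headline outcome. There are three incompatible statements of what is primary: the CAP count; the kits-plus-ARI count; and the CAP count together with provider preference. Provider choice is secondary in two places and primary in a third. No sentence says which governs, so the primary result could be named after the data are seen.

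This conclusion rests on the wording alone. Its numerical size cannot be fixed from the document. The 1.5% to 9% range is an illustration that assumes a pneumonia share of 5% to 30% and no change in other ARI care-seeking. The false-positive figures in the working assume particular correlations between outcomes. Because the conflict concerns the primary outcome itself, it needs correcting before results are interpreted.

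**What to change.** Name one primary outcome, with its condition, treatment source, unit and data source. Use it in the Abstract, Study aim, Post intervention phase and both paragraphs of the Data management & analysis plan. The natural choice is the trial's own CAP count, which already appears in the Abstract, in Study aim and as item (a) of the later analysis paragraph. Make the kits-plus-ARI count and provider choice secondary; Study aim and the statistical-tests paragraph already place provider choice there.

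If the CAP count and provider preference are both to stay primary, state a multiplicity rule that covers both outcomes and all three arm-versus-control contrasts, that is 2 × 3 = 6 tests. Adjusting across the two outcomes alone would leave the three contrasts unadjusted.

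The cost is mainly wording, plus a check that the registry entry agrees. The CAP count will have fewer events than the ARI-inclusive count and will probably rely more on filled-in diagnoses, so the number filled in should be reported by arm. A once-per-episode counting rule would need linkage across facility records, while Ethics and research governance says respondents' identifiers will not be recorded. It should therefore not be added without settling how the linkage would work.

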##### Quarterly health facility audit

This will be done to collect data on process Indicators and will be used for the establishment of Management information-system. Process indicators will be (i) utilization of PDK, PMC and (ii) conduct of PAS sessions in APHC, CHC and during VHND as well as numbers attending it. This will be done by the project staff. Data will be abstracted from records of PHC/CHC and SC for number of clinical pneumonia treated either as outpatients or inpatients or referred (with reasons and place) in last 1 month, and utilization of PDK and availability of medicines and equipment for the treatment of CAP (both provided through the project and supplied from the government). This information will be collated and shared with the Medical officer-In Charge of the health facility, Chief Medical Officer of Lucknow and office of Mission Director, National Health Mission.

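### The primary outcome is defined in two incompatible ways, and the version that adds kits to children can count one child's illness more than once

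*Protocol article*

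**What the plan says.** The protocol article words the facility-based outcome in three places.

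- **Study aim:** "Outcome measure will be number of CAP treated by ANMs/doctors with medicines from PDK or treated at either PMC or PMU". The unit is a case of CAP, and the conditions are joined by *or*.
- **Data management & analysis plan, paragraph on statistical methods:** "number of PDK kits distributed to children plus the number of children treated by government functionaries" and, continuing, "for acute respiratory infection (ARI) or pneumonia without PDK, using medicines available at the health facility". The first term counts kits, the second counts children, and the two are added. The diagnosis in the second term is ARI or pneumonia, which is wider than CAP.
- **Data management & analysis plan, later paragraph listing the primary outcomes:** "number of patients of CAP treated by ANMs/doctors with medicines from PDK OR treated PMC OR PMU". The unit is a patient, the diagnosis is CAP, and the conditions are again joined by *or*.

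The data come from the Quarterly health facility audit: "Data will be abstracted from records of PHC/CHC and SC for number of clinical pneumonia treated either as outpatients or inpatients or referred". Ethics and research governance adds that respondents' identifiers will not be recorded in any data collection instrument. Process indicators already lists distribution and utilization of kits as process measures.

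**The concern.** An *or* definition counts a patient once, however many of the conditions that patient meets. A sum of kits and children does so only if nobody receives a second kit and nobody appears in both terms. The protocol builds in routes by which a child can have more than one government contact in an illness. ANMs dispense kits and are trained to refer. APHCs hold kits and also stabilize and refer. The card in each kit tells caregivers how to watch for deterioration.

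If the sum is used, the count is of kits and treatment records, not of children reached. The planned analysis compares proportions between arms, and a numerator with repeat entries is not a number of distinct children. The comparison is biased if repeat contact differs by arm. That is plausible, because the awareness sessions teach danger signs and when and where to seek care, and the usual-care arm receives no such sessions. The documents do not quantify it.

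**Working it through.** The protocol states no expected count, sample size or re-contact rate for this outcome, so there is no figure of its own to reproduce. The check has two parts.

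**1. Apply the definitions to the same child**

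| Course of one illness | Kits plus children | Patients meeting any condition |
|---|---|---|
| One kit, no further contact | 1 | 1 |
| One kit, later a second kit | 2 | 1 |
| One kit, later facility medicines at a Pneumonia Management Unit | 1 or 2 (see below) | 1 |
| One kit, then referred but not treated again | 1 | 1 |
| ARI that is not CAP, treated with facility medicines, no kit | 1 | 0 |

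The third row depends on how the restriction to treatment without a kit is applied. Applied per child, it excludes a child who already had a kit, and the count is 1. Applied per visit or per facility record, the later treatment was given without a kit, and the count is 2. To apply it per child, the later facility's record must show the earlier kit. The audit abstracts numbers from separate sub-centre, PHC and CHC records, and no linking identifier is described.

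**2. Size under assumed rates**

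Let *N* be the number of children treated, *k* the share first treated with a kit, and *r* the share of those counted again (a second kit, or facility medicines recorded as a new child). Then:

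recorded count = *N* × (1 + *k* × *r*)

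Both *k* and *r* are assumptions. For *N* = 1000:

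- *k* = 1: *r* = 2%, 5%, 10%, 20% gives 1020, 1050, 1100, 1200.
- *k* = 0.5: *r* = 5%, 10%, 20% gives 1025, 1050, 1100.

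For two arms with the same true number of children and the same *k*:

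ratio = (1 + *k* × *r*₁) / (1 + *k* × *r*₀)

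With *k* = 1:

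- 5% v 5%: 1.05/1.05 = 1.00
- 10% v 5%: 1.10/1.05 = 1.048
- 15% v 5%: 1.15/1.05 = 1.095
- 20% v 5%: 1.20/1.05 = 1.143

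With *k* = 0.5 the effect is about half as large: 10% v 5% gives 1.05/1.025 = 1.024, and 15% v 5% gives 1.075/1.025 = 1.049. If the rates ran the other way, 5% v 10% with *k* = 1 gives 1.05/1.10 = 0.955.

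**The case against.** The strongest defence is that the sum is written as a partition: children treated with a kit, plus children treated without one. By the Medicines section a kit holds one child's course, so one kit stands for one treated child, and the restriction in the second term keeps the groups apart. On that reading nobody is counted twice unless a second kit is given. This is fair. It means that double counting is possible, not certain. It does not remove the second-kit problem, and the protocol does not show how the restriction could be applied per child from separate facility records.

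A second defence is that this is a journal article, and that the full protocol, procedures or case sheet may contain a de-duplication rule. That also stands: the lack of such a rule here is not in itself a fault. But the conflict between the definitions, and the addition of kits to children, are in the printed text. The home visits to about 5% of kit recipients (Adverse events monitoring) also suggest that some traceable record exists, so linkage may be more feasible than the text on identifiers implies.

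Four stronger readings are tempting, and the documents do not support them.

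- **A referral is counted at both facilities.** The audit records referred cases, with reasons and place, but the sum counts kits and children treated. A referral alone adds nothing; re-treatment or another kit does.
- **Treatment failure is scored as success.** Post intervention phase describes the outcome as use of public facilities, not cure. A return to public care is still use; the fault is counting it as another child.
- **Cases are credited to the facility's arm and not to the child's block.** No section says how cases are credited.
- **The count favours the awareness-session arms.** Equal rates cancel. Early recognition, which the sessions also teach, could reduce repeat contact.

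The survey outcome on provider preference does not depend on facility counts and is not affected.

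**Conclusion.** The point holds as an inconsistency in a stated primary outcome, with a possible miscount. The Study aim and the later outcome paragraph count CAP cases or patients once across three conditions. The statistical-methods paragraph adds kits to children and widens the diagnosis to ARI. The results differ when a child receives a second kit, when a child is re-treated with facility medicines after a kit and the record is not linked, and when ARI that is not CAP is treated.

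The size cannot be derived from the documents. Under assumed re-count rates of 2% to 20%, the sum exceeds the number of children by 2% to 20% if all start with a kit, and by less otherwise. Between arms, the illustrative ratios of 1.05 (10% v 5%) and 1.10 (15% v 5%) rest on assumed unequal rates, equal true numbers and every child starting with a kit. Equal rates give 1.00. A reader might infer that the planned comparison is known to be biased; the text shows only that it is open to bias that the described records could not detect.

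**What to change.** Use one definition in the Study aim and in both paragraphs of the Data management & analysis plan: illness episodes in children under 5 with at least one government treatment, each counted once at first contact. State the same diagnosis in all three places, either CAP or ARI/pneumonia, and fix in advance the interval within which further contacts belong to the same episode.

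Mark repeat and referred-in contacts on the project case sheet and the ANM kit record with a coded, non-identifying episode or referral number, which respects the rule on identifiers, and leave them out of the count. Report kits distributed, already listed under Process indicators, and referrals, already collected in the audit, as process measures only.

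The cost is a small recording burden and a slightly lower headline count. Linkage will not be complete: Table 1 lists 331 functional sub-centres, 28 APHCs and 9 CHCs, and the case sheet is described for doctors only. The share of contacts that could not be linked should therefore be reported by arm.

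### Filling missing diagnoses with one proportion per arm and month can create a false difference between arms in the non-PDK part of the primary outcome

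*Protocol article*

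**What the plan says.** All of this stands in the protocol article under Data management & analysis plan.

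- The primary outcome there is the number of kits distributed "plus the number of children treated by government functionaries for acute respiratory infection (ARI) or pneumonia without PDK". Only the second part depends on a recorded diagnosis.
- Where the diagnosis is missing, "we fill this missing information by extrapolation from data where diagnosis is given for the same month and within the intervention arm". The plan gives its premise for this step in the same sentence: "assuming that there would be similar proportion of cases with this diagnosis".
- The next sentence is the primary contrast: "We will compute the difference in the proportion of ARI/pneumonia treated in each intervention arm when compared to control arm". The comparison is made "using tests of proportion", and a p value below 0.05 "will be taken as statistically significant, using a two tailed distribution".
- For facility utilization, "the data will be abstracted periodically from the records maintained there". The quarterly audit section names PHC/CHC and sub-centre records as the source.
- On extreme values: "Outliers will be identified, reported and excluded from analysis if required".

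Under Study design, each arm consists of two blocks and the trial is open label.

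**The concern.** The rule stratifies by arm and month only. Within an arm it pools two blocks and three levels of care (sub-centre, APHC, CHC). It is right only if children without a recorded diagnosis have the same ARI/pneumonia share as those with one in that arm and month.

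The article gives reasons to doubt this. Table 3 and the training section send sicker children up from ANM and APHC to CHC, so the mix of patients may differ by level. The case sheet that doctors are trained to complete is for CAP patients, so recording may depend on the diagnosis. Project staff attend and document monthly sessions at APHCs and CHCs in Interventions 1 and 3 only, so record-keeping there could differ from the other two arms.

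If share and completeness both vary by level, and completeness also varies by arm, the fill turns a difference in record-keeping into a difference in cases. No step that allows for the filled values is stated between the fill and the test. If they are treated as observed, the standard error is too small even when the assumption holds. The comparison at risk decides which communication strategy is scaled up.

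**Working it through.** The plan states no missing fraction and no expected count, so there is no figure to reproduce. The inputs below are assumptions, chosen to show the mechanism.

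**1. Recording depends on facility level.** Assume 1,000 children treated without a kit in each arm: 500 at CHCs (30% ARI/pneumonia, all recorded) and 500 at lower levels (15%), with the same rates every month. The true count is 500 × 0.30 + 500 × 0.15 = 225 in every arm.

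The filled count is recorded cases + missing × (recorded cases / recorded children).

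| Lower-level completeness | Recorded children | Recorded cases | Proportion | Filled count |
|---|---|---|---|---|
| 80% | 500 + 400 = 900 | 150 + 60 = 210 | 23.3% | 210 + 100 × 0.233 = 233.3 |
| 20% | 500 + 100 = 600 | 150 + 15 = 165 | 27.5% | 165 + 400 × 0.275 = 275.0 |
| 90% | 500 + 450 = 950 | 150 + 67.5 = 217.5 | 22.9% | 217.5 + 50 × 0.229 = 228.9 |
| 50% | 500 + 250 = 750 | 150 + 37.5 = 187.5 | 25.0% | 187.5 + 250 × 0.25 = 250.0 |

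The false ratios are 275.0/233.3 = 1.18 and 250.0/228.9 = 1.09.

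**2. Dilution by kits.** Add the same number of directly counted kits to each arm.
- 225 kits: 458.3 v 500.0, ratio 1.09. Milder case: 453.9 v 475.0, ratio 1.05.
- 675 kits: 908.3 v 950.0, ratio 1.05. Milder case: 903.9 v 925.0, ratio 1.02.

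**3. Filling within facility level.** The lower-level share among recorded children is 60/400 = 15% in one arm and 15/100 = 15% in the other. The filled counts are 210 + 100 × 0.15 = 225 and 165 + 400 × 0.15 = 225, so the false difference disappears.

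**4. Recording depends on the diagnosis itself.** Let p be the true share, rA the probability that an ARI/pneumonia diagnosis is recorded, and rN that for other children. The filled share is p·rA / (p·rA + (1 − p)·rN). With p = 0.30 and both rates 70%, it is 30%. If one arm records ARI/pneumonia at 85%, it is 0.255/(0.255 + 0.490) = 34.2%, a false gap of 4.2 points (ratio 1.14, or 1.07 if half of all cases are kit cases). Finer strata do not remove this.

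**5. Fill assumption true, filled cases treated as observed.** With a fraction m missing, the true variance rests on N(1 − m) children but the test uses N. Its two-sided error is 2 × [1 − Φ(1.96 × √(1 − m))]: 6.3% at m = 10%, 10.1% at 30% and 16.6% at 50%, against a nominal 5%. Simulation (40,000 runs, 1,000 children per arm) gave 9.9% and 16.5% at the last two. Children are treated as independent here. Clustering by block would change these rates but not the biases in steps 1 and 4.

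**The case against.** - **Kits need no diagnosis.** This stands. Kits go to ANMs, APHCs and CHCs and are replenished, and ANMs at the sub-centres are trained to treat from them. A reader might take 18% as the error in the whole primary outcome. It applies only to the part treated without a kit, and step 2 shows how it shrinks.
- **Training and infrastructure are common to all arms.** This also stands. A reader might infer that training on pneumonia records makes completeness differ by arm. The documents do not support that, because usual care gets the same training, kits and audit. Project presence at facilities in two arms is a possible cause, not a demonstrated one.
- **The shares by level are invented.** They are assumed. Table 3 describes severity triage within pneumonia, not the ARI/pneumonia share among treated children.
- **Variance handling may sit in an unseen analysis plan.** That is possible. Treating filled values as observed is the natural reading of the text but remains an inference. The fill rule itself is stated in the article, so it can be judged here. Filling by arm and month does already respect season and arm.
- **Outliers will be reported, and a criterion may exist elsewhere.** This largely stands. A reader might infer that analysts who know the arm will remove inconvenient counts, or that the sentence contradicts intention to treat. Open label does not show that analysts are unblinded, and no stated rule removes or reassigns an allocated block.

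**Conclusion.** The concern holds in a bounded form. The fill rule, as fixed, can produce a difference between arms in the non-PDK part of the primary outcome with no true effect. For recording that follows facility level, two conditions must both hold: the ARI/pneumonia share differs by level, and completeness differs by level and by arm. The size is then 18% or 9% of the non-PDK count under the two assumed scenarios, falling to 9% or 5% with 225 kits per arm and to 5% or 2% with 675. Recording that depends on the diagnosis, to a degree that differs by arm, has the same effect by another route.

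If diagnoses are missing at random within arm and month, the point estimate is unbiased, and the remaining fault is overstated precision if filled cases are treated as observed. The documents do not show which situation applies, so the finding is a risk and not a predicted bias. The outlier sentence is a secondary matter of wording.

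**What to change.** 1. Fill missing diagnoses within block × facility level × month, merging months where cells are sparse. Over 12 intervention months this is 8 × 3 × 12 = 288 cells, against 4 × 12 = 48 under the present rule. Age strata are not proposed, because the audit as described may not hold the records for them.
2. Carry the uncertainty of the filled values into the standard error, for example by multiple imputation.
3. Report beside it the count from recorded diagnoses only and the bounds with all or none of the blanks counted as cases. These are needed because stratifying does not help when recording depends on the diagnosis. They are checks, not replacements: in the first scenario the recorded-only counts are 210 v 165, which errs the other way, and the bounds are 210 to 310 and 165 to 565, both of which contain 225.
4. Reword the outlier sentence so that all verified values stay in the primary analysis and exclusion is a sensitivity analysis.

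The cost is a few sentences, modest extra programming and slightly wider intervals. The abstraction must also note, by facility and month, how many treated children have no diagnosis.
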